## Abstract

**Background:**

Breast fibroadenomata (FAD) are the most common benign lesions in women. For palpable lesions, there are currently three standard treatment options: reassurance (with or without follow-up), vacuum-assisted mammotomy (VAM) or surgical excision. High-intensity focused ultrasound (HIFU) ablation has been used in the treatment of FAD. The drawback of HIFU is its prolonged treatment duration. The aim of this trial is to evaluate circumferential HIFU treatment for the effective ablation of FAD with a reduced treatment time.

**Methods/design:**

Fifty patients (age ≥18 years) will be recruited with symptomatic FAD, visible on ultrasound (US, grade U2 benign). In patients ≥25 years, cytology or histology will be performed to confirm the diagnosis of a FAD. These patients will receive HIFU treatment using the US-guided Echopulse device (Theraclion Ltd., Malakoff, France) under local anaesthesia. An additional 50 patients will be recruited and contacted 6 months after discharge from the breast clinic. These patients will be offered an US scan to determine the change in size of their FAD. This natural change in size will be compared to the decrease in size after HIFU treatment. Secondary outcome measures include post-treatment complications, patient recorded outcome measures, mean treatment time and cost analysis.

**Trial registration:**

Current Controlled Trials: ISRCTN76622747.

## Background

Fibroadenomata (FAD) are the most common benign breast lesions in women. FAD can occur at any age but are most common between 20 and 30 years of age. FAD occur in about 10% of all woman and account for about 50% of all breast biopsies performed [1]. Studies revealed that up to 59% of FAD will show regression or complete resolution within 5 years [1]. Malignant transformation within FAD is considered exceptionally rare (0.002%–0.0125%) and there is a 1.3–2.1 increased risk of breast cancer in women with FAD compared to the general population [2]. FAD are encapsulated from their surrounding tissues and can be considered as an aberration of normal breast development rather than a true neoplasm. On histology, FAD consist of combined proliferation of epithelial and fibroblastic tissue elements which are slowly growing and oestrogen dependent [3,4].

The diagnosis of a FAD can be made by standard triple assessment (clinical examination, imaging and histopathology). During clinical examination, 50%–67% of breast lesions identified as a FAD are confirmed as FAD on imaging and/or histopathology due to similar characteristics with other benign conditions [5,4]. Therefore, more accurate diagnostic methods are required to get the correct diagnosis. Ultrasound (US) is the main diagnostic imaging modality used for the diagnosis of FAD [5], and fine needle aspiration cytology (FNAC) or core needle biopsy (CNB) can be used to get tissue confirmation of the diagnosis. The overall diagnostic accuracy of this triple assessment is approximately 70%–80%, but an accurate differentiation between a benign and a malignant lesion is provided in 95% [5,4].

The management of non-palpable FAD is conservative with reassurance. For palpable FAD, there are currently three main treatment options available: reassurance (with or without follow-up), vacuum-assisted mammotomy (VAM) and surgical excision. VAM is not officially licensed for the treatment of FAD only to obtain the diagnosis of a lesion. Intervention is normally offered to patients with large FAD or rapidly growing lesions or to patients requesting excision of the lesion due to anxiety, discomfort or breast distortion [4]. In other cases, surgical removal can cause scarring and poor cosmetic outcome [5,6].

A new technique in the treatment of FAD is high-intensity focused ultrasound (HIFU) ablation. This is a non-invasive ablative technique in which the FAD is treated with focused consecutive repeated US pulses, while surrounding tissues are protected from the applied heat.

The basis of HIFU therapy is a HIFU pulse of several seconds generated by a piezoelectric US transducer. The US field is insonated via a coupling media overlaying the tissue to the targeted area. Due to the high local concentration of acoustic energy in the focal spot, the tissue in a small volume is heated rapidly, and a sharp circumscribed lesion caused by thermal coagulation will be induced [7]. HIFU has been clinically applied for the treatment of invasive breast cancer and demonstrated coagulative necrosis on pathological assessment, regression of tumour size and loss of proliferative activity with a minimal side effect profile [8-16]. Pathological examination with Victoria Blue and Ponceau histochemical staining has been used to assess tumour vascular wall destruction and immunohistochemical staining for proliferative markers using biotin-streptavidin-peroxidase [13]. Cell viability has been determined by staining for active dehydrogenase using 2,3,5-triphenyltetrazolium chloride (TTC) [14].

The current limitation of HIFU is the prolonged treatment duration associated with the procedure. Since a single pulse generates a rather small tissue lesion, a lot of these consecutive repeated pulses have to be applied with an adequate idle time in between to prevent overheating and damage to normal tissue [7]. We propose to overcome the prolonged treatment duration by applying HIFU pulses to the circumferential surface area of the lesion rather than their whole volume. We propose to perform this upon a cohort of patients with benign breast tumours in the form of FAD using the US-guided Echopulse^TM^ (Theraclion Ltd., Malakoff, France) HIFU system, which is CE marked for the treatment of breast FAD.

## Methods/design

### Patients

We will undertake treatment on 50 patients with confirmed FAD. Patients will be identified in three ways: (1) at multidisciplinary meetings (MDM), where all patients who undergo CNB or FNAC are discussed; (2) patients scheduled for surgical excision of a FAD; and (3) patients visiting the Breast Clinic requesting surgical excision. All patients will be approached in the Breast Clinic or via telephone asking if they are interested in receiving a patient information sheet on the HIFU-F trial which describes the procedure in detail. If patients are interested, a second telephone call will be made to check if the patient would like to participate in the study and to answer any questions. Patients who are willing to participate in the study will provide informed written consent on the day of elective surgery or at a prior hospital visit (during pre-assessment). Details of all patients approached about the trial will be recorded on the patient-screening log and kept in the Investigator Site File.

### Inclusion and exclusion criteria

Patients eligible for this trial are patients ≥18 years of age with FAD diagnosed according to local hospital protocol visible on US (graded U2 benign). In patients ≥25 years of age, confirmation is required by either FNAC (C2) or CNB (B2) (Figure 1). The definitive diagnosis of FAD must be confirmed by the breast MDM.

**Figure 1 Fig1:**
[figure not shown]
HIFU-F trial scheme.

Exclusion criteria are FAD with atypia or suspicion of phyllodes (graded B3/C3 or greater), pregnant or lactating women, women with breast implants and women with a history of laser or radiation therapy to the targeted breast.

### Control group

Another 50 patients with symptomatic palpable FAD who have been discharged from the Breast Clinic since the HIFU-F trial started (12 December 2013) will be recruited. These patients will be contacted 6 months after their discharge and will be offered an US scan in order to determine the change in volume of their FAD.

This cohort will be selected in order to identify the natural course of FAD over a period of 6 months from diagnosis. Analysis will be performed to compare the difference in volume between the HIFU-treatment group *versus* control group initially when 20 control patients have been recruited.

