## Discussion

At our unit, over 600 FAD were identified on US imaging in 2012 of which 6 underwent VAM and 60 formal surgical excision. Difficulties could be encountered during recruitment of patients from the MDM. Clinicians could be hesitant to allow recruitment of patients who have symptomatic FAD, but would not generally be offered intervention. Patients offered surgical excision are usually patients with atypical FAD, lesions with a suspicion of phyllodes tumour and fast growing and large FAD. Most of these patients are not eligible for HIFU treatment and should be offered surgical excision. Large lesions are not an exclusion criteria, but HIFU treatment would take significantly longer and multiple treatments might be needed to treat the whole FAD.

In general, FNAC and CNB could be performed in all patients; however, local protocol permits women <25 years of age in which US and physical examination reveals a solid lesion with typical benign characteristics to omit histopathology. This is due to the low incidence of breast cancer in woman of this age group [17,18].

The primary outcome measure is the volume decrease of the FAD as visible on US. US is the standard diagnostic imaging modality for FAD and accessible to patients and staff. Furthermore, the FAD must be visible on US to be eligible for HIFU; it should therefore be possible to visualise and measure the FAD post-treatment as well. Disadvantages of US as an imaging modality are the inter-observer variability between the measurements performed by different ultrasonographers. The ideal imaging modality would be accessible and overcome inter-observer variability.

In this protocol, the diameters of the FAD are measured in three dimensions to calculate the volume of the FAD with formula (1), in which A, B and C are the largest diameters in the three dimensions.1$$ V\kern0.5em =\kern0.5em \frac{4}{3}\kern0.5em \times \kern0.5em \pi \kern0.5em \times \kern0.5em \left(\frac{1}{2}A\right)\kern0.5em \times \kern0.5em \left(\frac{1}{2}B\right)\kern0.5em \times \kern0.5em \left(\frac{1}{2}C\right) $$

Measuring one diameter is not sufficient since the decrease enough since the decrease in size could be different in the different dimensions, and with the volume, these are all taken into account.

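### Controls are first approached, and offered an optional outcome scan, after their six-month change has occurred, so the comparison is open to participation bias that the planned t-test cannot remove

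*Protocol article*

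**What the plan says.** The Control group section of the protocol article defines the comparison arm as "Another 50 patients with symptomatic palpable FAD who have been discharged from the Breast Clinic" since the trial opened on 12 December 2013. On recruitment it says: "These patients will be contacted 6 months after their discharge and will be offered an US scan". The arm's purpose is then stated: "This cohort will be selected in order to identify the natural course of FAD over a period of 6 months from diagnosis".

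The treated arm is handled differently. Under Patients, "We will undertake treatment on 50 patients with confirmed FAD"; these women give written consent on the day of the procedure or at an earlier visit. Under HIFU treatment group, they have ultrasound at 2 weeks and at 3, 6 and 12 months.

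The eligibility rule under Inclusion and exclusion criteria begins: "Patients eligible for this trial are patients ≥18 years of age with FAD diagnosed according to local hospital protocol visible on US". It does not mention palpability.

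Under Outcome measures, the primary outcome is change in lesion volume on ultrasound. The two groups are compared with a two-sample t-test, preceded by an F-test of the variances. The article mentions no adjustment for baseline differences or for non-attendance.

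**The concern.** A woman enters the control data only if she accepts a scan offered at the end of the observation window. If acceptance depends on how her lump has behaved, the scanned women do not represent the discharged women. Someone with a persistent or growing lump plausibly has more reason to attend than someone whose lump has faded. In that case natural regression is understated and the HIFU effect overstated. HIFU patients commit before their outcome exists, so at enrolment the problem affects one arm only.

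The control arm exists to measure natural change, and the Background treats that change as appreciable (regression or resolution in up to 59% within five years). A distortion of the control mean passes directly into the primary comparison, and recruiting more controls by the same route does not reduce it.

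A second, separate matter is comparability at baseline. Controls must have palpable lesions, while the eligibility rule asks only for visibility on ultrasound.

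**Working it through.** The protocol gives no power calculation, SD or expected control change, so there is no figure to reproduce. The two illustrations below show the scale of the problem; neither is an estimate.

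**1. Bias in percentage points**

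From the Background: up to 59% regress or resolve within five years, which is ten half-years.

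- Linear: p = 0.59 / 10 = 0.059.
- Constant hazard: p = 1 − (1 − 0.59)^(1/10) = 0.0853.

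Assumed: regressing lesions lose 60% of volume, the others grow 5%, and women with regressing lesions attend at half the rate of the others.

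- True mean = p × (−60) + (1 − p) × 5.
- Share regressing among those scanned: p′ = 0.5p / (0.5p + 1 − p).
- Bias = observed mean − true mean = 65 × (p − p′).

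| p | True mean | p′ | Observed mean | Bias (points) |
|---|---|---|---|---|
| 0.059 | +1.2% | 0.0295 / 0.9705 = 0.0304 | +3.0% | 65 × 0.0286 = 1.9 |
| 0.0853 | −0.5% | 0.04265 / 0.95735 = 0.0446 | +2.1% | 65 × 0.0407 = 2.6 |
| 0.20 (assumed) | −8.0% | 0.1 / 0.9 = 0.1111 | −2.2% | 65 × 0.0889 = 5.8 |

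In all three rows the bias favours HIFU. If attendance is reversed (women with regressing lesions twice as likely to attend), p′ becomes 0.111 and 0.157 in the first two rows. The bias is then about 65 × (0.059 − 0.111) = −3.4 and 65 × (0.0853 − 0.157) = −4.7 points, against HIFU.

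**2. Effect on the t-test**

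Assumed: two-sided 5% level, unit SD in both groups, no true HIFU effect, and about 50% scan uptake following a logistic model in standardised volume change. With 50 v 50 the standard error is √(1/50 + 1/50) = 0.20 SD. The chance of a significant result is Φ(b/0.20 − 1.96) + Φ(−b/0.20 − 1.96), where b is the bias in SD units.

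| Uptake odds ratio per SD (assumed) | Bias b (SD) | False-positive rate, 50 v 50 |
|---|---|---|
| 1.0 | 0 | 5% |
| 1.5 | 0.20 | 16% |
| 2 | 0.31 | 35% |
| 3 | 0.44 | 60% |

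For scale, 50 v 50 has 80% power for 0.56 SD: (1.96 + 0.84) × 0.20. With 50 HIFU patients against the 20 controls of the first planned comparison, the last three rates are 11%, 22% and 38%. Adding controls makes the false-positive rate worse because the bias stays while the standard error falls. No SD is given, so the SD and percentage-point scales cannot be converted into each other.

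**3. The control clock**

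Contact is timed from discharge, but the stated aim is timed from diagnosis. The two agree only if diagnosis and discharge fall on the same day.

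**The case against.** The strongest reply is that the source cohort is fixed by discharge, which precedes the outcome, and that nothing in the protocol shows attendance to depend on volume change. That is right as far as it goes. A reader might infer that the control arm is selected on outcome. The document does not support this: only acceptance of the scan can depend on the outcome, feeling a lump is not the same as knowing its ultrasound volume change, and the direction of any bias is not fixed. The different definition of controls raises a question of baseline comparability and is not evidence of selection on outcome.

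Other stronger readings also fail:

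- **Symptoms.** The Abstract describes the HIFU group as symptomatic, so the clear mismatch is palpability alone.
- **Tissue confirmation and exclusions.** These stand in a general section before both group descriptions and read as trial-wide. That the Control group section does not repeat them is no sign that they do not apply.
- **Pregnancy and lactation.** The exclusion of "pregnant or lactating women, women with breast implants" is an entry criterion and is not re-applied to HIFU patients at six months either. A check at the control scan alone would create a new difference between the arms.
- **Supply of controls.** The Discussion says "over 600 FAD were identified on US imaging in 2012 of which 6 underwent VAM and 60 formal surgical excision". Subtracting 66 from 600 leaves 534, but this counts lesions, not eligible women with palpable symptomatic ones, so it does not show that comparable controls are plentiful.

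It is also fair that 2 to 2.6 points is small beside the 50% volume reduction that the protocol uses as its benchmark at six months. A screening log for all patients approached is already described under Patients. What survives is the recruitment rule itself: the protocol states it, applies it to one arm only, and the planned test cannot correct it.

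**Conclusion.** The concern holds as a risk of outcome-related participation bias in the control mean, probably but not certainly in HIFU's favour. With the protocol's own upper regression figure and the assumed shrinkage, growth and attendance, it amounts to about 2 to 2.6 percentage points. The figure of about 6 points needs an assumed 20% regression share that the documents do not supply. The false-positive rates of 16% to 60% rest on assumed uptake odds ratios of 1.5 to 3 per SD and show only that moderate dependence would matter to the test. Two lesser points stand beside it: baseline comparability is not assured, because palpability is required of controls only, and the two starting points of the control clock must be reconciled. The change should be made while controls are still being recruited, since the status of women who decline is hard to recover later.

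**What to change.** - For women not yet discharged, invite consecutive eligible women at discharge to a booked six-month scan, so that agreement comes before the outcome.
- For women already discharged, approach in discharge-date order.
- State that the screening log covers controls. Record baseline volume and age for everyone approached, compare attenders with non-attenders, and weight if they differ. Weighting on these two variables corrects only the part of the selection that they explain, which is why booking at discharge matters more.
- Use the same palpability wording for both groups.
- Give the control interval one starting point in place of discharge in one sentence and diagnosis in another.

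The cost is protocol wording, a fuller log, slightly slower control recruitment and some added analysis. No extra scans are needed. Frequency-matching on volume or age is a trade-off against consecutive invitation and is not required for this correction.

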### Outcome measures

The primary outcome measure is the change in volume of FAD as recorded by US. Secondary outcome measures will include complications, patient-recorded outcome measures, mean treatment time and cost-effectiveness of the HIFU treatment compared to surgical excision.

All patients will be asked prior to receiving HIFU treatment and again at 6 and 12 months post-treatment to submit sections of the Breast-Q Breast Conserving Therapy Modules to assess patient-recorded outcome measures.

A two-sample *T*-test will be performed to determine if there is a significant difference in FAD volume reduction between the study group and the control group. To determine if the variances are equal or unequal, we will perform a two-sample *F*-test. A two-sample *T*-test will also be used to determine if there is a significant reduction in lesion volume at 6 months compared to prior to treatment.

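### The primary comparison is an unadjusted t-test between non-randomised groups with different indications, on a reduction scale that is not fixed, so a difference in baseline volume could pass for a HIFU effect

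*Protocol article*

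**What the plan says.** The Outcome measures section of the protocol article defines the endpoint: "The primary outcome measure is the change in volume of FAD as recorded by US". The groups are to be compared by a two-sample t-test for a "significant difference in FAD volume reduction between the study group and the control group", with an F-test on the variances to choose between the equal- and unequal-variance forms. No covariate, matching or stratification is named. The section does not say whether reduction is in cm3 or as a percentage of baseline.

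The groups are not randomised.

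- **HIFU group (Patients section):** "We will undertake treatment on 50 patients with confirmed FAD". They are found by three routes: MDM lists of women who had needle sampling, "patients scheduled for surgical excision of a FAD", and women who come to the clinic asking for excision.
- **Control group (Control group section):** "Another 50 patients with symptomatic palpable FAD who have been discharged from the Breast Clinic" after the trial opened, with a first comparison "initially when 20 control patients have been recruited".

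Three other places bear on lesion size. The Background says "Intervention is normally offered to patients with large FAD or rapidly growing lesions", and also to women who ask for removal. The Inclusion and exclusion criteria contain no size or growth rule. The Discussion states that large lesions are not excluded. It also says that most of the women usually offered excision (atypical, suspicious, fast-growing or large lesions) are not eligible for HIFU.

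**The concern.** The two groups reach the study by different clinical decisions: intervention planned, requested or discussed at the MDM on one side, discharge on the other. Those decisions plausibly relate to lesion size. If HIFU lesions start larger and all lesions shrink somewhat on their own, the HIFU group loses more cm3 even if HIFU does nothing. An unadjusted t-test on absolute reduction cannot tell this apart from a treatment effect.

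Natural shrinkage is to be expected. The Background cites regression or resolution of up to 59% of lesions within 5 years, and the control group exists to measure it.

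There is also a loss of precision. Volume is a product of three diameters (formula 1 in the Discussion), so it tends to be right-skewed, and absolute change inherits the spread of the starting volumes. At stake are a false-positive primary result if baselines differ and lost power if they do not.

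**Working it through.** The protocol article gives no alpha, power, standard deviation or effect size, so there is no planned figure to reproduce. The check asks how the stated test behaves when HIFU has no effect.

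**Inputs from the documents:** 50 v 50 patients; two-sample t-test; no adjustment.

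**Assumed inputs:** two-sided 5% test; lognormal baseline volume with log-SD σ = 0.9; log change with SD τ = 0.3; the same geometric-mean shrinkage s in both groups, varied over 10%, 20% and 30%; HIFU:control ratio r of median baseline volume of 2 or 3.

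**Model:** 6-month volume = baseline × (1 − s) × exp(e), with e normal, mean 0 and SD τ.

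**Expected spurious difference.** With the control median as unit, mean absolute reduction in a group with median m is m × exp(σ²/2) × [1 − (1 − s) × exp(τ²/2)].

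- exp(0.81/2) = 1.499 and exp(0.09/2) = 1.046.
- At s = 20%: 1 − 0.80 × 1.046 = 0.163.
- Controls (m = 1): 1.499 × 0.163 = 0.24. HIFU at r = 2: 0.49. HIFU at r = 3: 0.73.
- Apparent HIFU benefit with no effect: 0.24 control-median volumes at 2:1 and 0.49 at 3:1.

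**Simulated false-positive rate, Welch t-test on absolute reduction** (thousands of runs per setting; repeat runs differ by a few points):

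| Common shrinkage | Ratio 2:1 | Ratio 3:1 |
|---|---|---|
| 10% | about 7% | about 11% |
| 20% | about 26% | 46–49% |
| 30% | about 53% | about 84% |

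On the same inputs, ANCOVA of log 6-month volume on group and log baseline stays at about 5%, and a t-test on percent reduction at 4–6%. At the first look with 20 controls and 20% shrinkage, the absolute t-test rejects in about 24% (2:1) and 43% (3:1).

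**Other assumptions.** With baseline CV 0.6 and proportional change with SD 25 points, the absolute t-test rejects in 18%, 54% and 82% of runs at 2:1, and 32%, 84% and 99% at 3:1, for 10%, 20% and 30% shrinkage. At a ratio of 1.5 the figures are 10%, 21% and 41%; with equal baselines, 4–5%. Log ANCOVA holds at 4–5% throughout.

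**Power with equal baselines** (true reductions 30% v 5%, σ = 0.9, τ = 0.4): about 70% for the absolute t-test, 95% for the percent t-test and 96% for log ANCOVA.

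**If natural growth differs.** Take the CV 0.6 set, ratio 2:1, 20% control shrinkage, no HIFU effect, and HIFU lesions with a natural course 10 points worse. The absolute t-test rejects in 5% of runs because the two biases cancel. The percent t-test rejects in 50% and log ANCOVA in 35%, both against HIFU. Under the log-SD 0.9 set, log ANCOVA rejects in about 45%. At 20 points worse (CV 0.6 set), the absolute t-test is itself biased against HIFU, with 57% rejections.

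**The case against.** A reader might infer from the Background that the HIFU group is selected on lesion size and growth, and so that the result is bound to favour HIFU. The documents do not support this. No eligibility criterion concerns size or growth. The first recruitment route is the MDM list of all women with needle sampling, and no proportions by route are given. The Discussion says most women usually offered excision are ineligible. It also contemplates recruiting women with symptoms who would not normally be offered intervention, which is close to the control population. Neither an imbalance nor its direction is established.

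The false-positive mechanism also needs the absolute scale. The one reduction threshold in the article, the 50% criterion for offering a further treatment, is relative. On a percent scale with proportional shrinkage the mechanical bias vanishes and power is nearly that of ANCOVA. The shrinkage rates and baseline ratios are assumed, and at 10% shrinkage the inflation is modest. Finally, faster natural growth in HIFU lesions would bias against HIFU, and baseline adjustment does not cure that; in one setting above it exposes a bias that the absolute test happened to cancel.

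All of this stands and limits the claim. It does not rescue the stated analysis. The article itself names an unadjusted test, so this is not detail left to an unseen plan. Large benign lesions remain eligible, so a size difference is plausible. Change in volume, read literally, is absolute, and the article writes a percentage where it means one. If percent was intended, the scale still has to be stated, because the test's validity depends on it.

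**Conclusion.** The point holds in a bounded form. The primary between-group test is unadjusted, compares non-randomised groups with different indications, and leaves the scale of reduction open. On the absolute scale, a baseline imbalance together with natural shrinkage can produce significance with no HIFU effect: about 7–53% of trials at 2:1 and 11–84% at 3:1, over 10–30% shrinkage, against about 5% for a log-scale adjusted or percent-change analysis. With equal baselines the cost is power, about 70% against 95–96% in the scenario examined.

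These figures rest on assumed distributions, shrinkage and ratios; the article gives no baseline volumes, so the actual imbalance is unknown. It would go too far to say that baseline confounding is present, that it must favour HIFU, or that adjusting for baseline volume makes the groups comparable.

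**What to change.** Fix the scale and adjust for baseline volume:

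- **Primary analysis:** a linear model of log 6-month volume on group, log baseline volume and age, reported as an adjusted ratio of geometric means with 95% CI. Unlike a percent-change t-test, it does not assume that shrinkage is proportional at every lesion size.
- **Non-visible lesions:** a small volume set in advance so that the logarithm exists, with a rank-based sensitivity analysis.
- **Supportive analysis:** keep the unadjusted t-test, with its scale stated.
- **Limitation to state:** confounding by prior growth and patient selection remains, can run in either direction including against HIFU, and is not removed by baseline adjustment.

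The cost is analysis wording only. Baseline volume is already needed to compute change, and age is needed for eligibility. The small downside is that the effect is reported as a ratio rather than in cm3.

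### A variance F-test is planned, evidently to choose the t-test version for the primary comparison; naming the Welch test outright is safer and costs essentially nothing (minor)

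*Protocol article*

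**What the plan says.** The Outcome measures section of the protocol article sets the endpoint: "The primary outcome measure is the change in volume of FAD as recorded by US". The analysis named for it is a t-test for two independent samples, which "will be performed to determine if there is a significant difference in FAD volume reduction between the study group and the control group". The next sentence adds the variance step: "To determine if the variances are equal or unequal, we will perform a two-sample" *F*-test. Neither the level of the F-test nor what follows from its result is spelled out. The only evident purpose is to decide between the pooled and the unequal-variance form of the t-test.

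The planned group sizes are equal. The Patients section says "We will undertake treatment on 50 patients with confirmed FAD", and the Control group section says "Another 50 patients with symptomatic palpable FAD who have been discharged from the Breast Clinic" will be recruited. The Control group section also plans a first comparison of the two groups "initially when 20 control patients have been recruited". It does not say how many HIFU patients that comparison will include.

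On the shape of the data, the Discussion computes volume as a product of three diameters and notes: "Large lesions are not an exclusion criteria". No SD, distribution or significance level is given.

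**The concern.** Three things make a preliminary variance test a poor way to pick the main test.

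- The F-test for variances assumes normal data. A volume formed by multiplying three diameters, with large lesions allowed in, is likely to be right-skewed. The F-test then reacts to skewness as well as to a difference in spread.
- When the F-test misses a real difference in spread, the pooled t-test is used where its standard error is wrong.
- The final p-value takes no account of the selection step.

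Unequal spread is plausible, because one group is ablated and the other follows its natural course. Unequal size is possible at the first comparison. If both occur together, the primary comparison does not run at its nominal level.

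**Working it through.** There is no stated figure to reproduce: the article gives no alpha, SD, effect size or power for this test. The check is therefore a simulation under the null.

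**Inputs from the article.** 50 HIFU patients and 50 controls planned; a first comparison at 20 controls.

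**Assumptions.** HIFU number at the first comparison between 20 and 50; t-test and F-test both at 5% two-sided; pooled t if F is not significant, otherwise Welch; SD ratios as shown.

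**Why size and spread must both differ.** The pooled standard error is based on s_p² × (1/n₁ + 1/n₂), with s_p² = [(n₁−1)s₁² + (n₂−1)s₂²]/(n₁+n₂−2). The correct variance of the difference is σ₁²/n₁ + σ₂²/n₂. If n₁ = n₂ = n, both estimates reduce to (s₁² + s₂²)/n. The pooled and Welch statistics are then identical and only the degrees of freedom differ, so it hardly matters which one the F-test selects.

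At 50 v 20 they separate:

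- HIFU SD 1, control SD 1.4. Correct variance: 1/50 + 1.96/20 = 0.118. Expected pooled value: (49 × 1 + 19 × 1.96)/68 × 0.07 = 1.268 × 0.07 = 0.0888. The pooled standard error is √(0.0888/0.118) = 0.87 of the true one, so it is too small.
- HIFU SD 1.5, control SD 1. Correct variance: 2.25/50 + 1/20 = 0.095. Expected pooled value: (49 × 2.25 + 19 × 1)/68 × 0.07 = 1.901 × 0.07 = 0.133. The ratio of standard errors is √(0.133/0.095) = 1.18, so it is too large.

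**Simulated type I error, normal data** (100,000 or more trials per row; figures rounded, and repeat runs differ by 0.1 to 0.2 points):

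| HIFU v control | SD HIFU : control | Two-stage rule | Welch |
|---|---|---|---|
| 50 v 50 | 1 : 1.4 | 5.0% | 5.0% |
| 20 v 20 | 1 : 1.4 | 5.0–5.1% | 5.0% |
| 50 v 40 | 1 : 1.4 | 5.3% | 5.0% |
| 30 v 20 | 1 : 1.4 | 5.6–5.8% | 5.1% |
| 40 v 20 | 1 : 1.4 | 6.3% | 5.0–5.1% |
| 50 v 20 | 1 : 1.4 | about 6.5% | 5.0% |
| 50 v 20 | 1.5 : 1 | 4.1% | 5.0% |
| 50 v 20 | 1 : 1 | 5.1% | 5.0% |

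In the 50 v 20 row with ratio 1 : 1.4, the F-test detects the inequality in only about 45% of trials. In the rest the pooled test is used, and that test taken alone has a type I error of about 8.9%.

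**Sensitivity of the F-test to shape.** With equal true variances it rejects in 5% of trials on normal data. It rejects in 27–29% on exponential data and in 39–46% on lognormal data with log-SD 0.8.

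**Whether Welch cures skewness.** On lognormal data (log-SD 0.8) at 50 v 20:

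- Control SD 1.4 times HIFU SD: Welch about 7.4%, two-stage rule about 6.8%.
- HIFU SD 1.5 times control SD: Welch about 4.4%, two-stage rule about 4.6%.
- Control SD twice HIFU SD: Welch 8.8%, two-stage rule 9.5%.

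Neither method is reliably closer to 5% there. At 50 v 50 on lognormal data the two agree to within 0.1 point.

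**The case against.** The strongest reply is that the planned design is 50 v 50, where the two-stage rule and Welch give the same error rate, so nothing is at stake in the main analysis. That stands. Modest loss of controls changes little either, as the 50 v 40 row shows.

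A reader might infer that the 20-control analysis itself breaks error control. The article does not support that. It does not say how many HIFU patients will be compared at that point, and at 20 v 20 there is no loss. Unequal sizes alone also do no harm: at 50 v 20 with equal SDs and normal data the rule runs at 5.1%.

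Nor is the direction known. Inflation needs the smaller control group to be the more variable one; if HIFU makes volume change more variable, the rule is conservative. The article gives no SDs to settle this.

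A reader might also infer that replacing the rule by Welch removes the effect of skewness. The lognormal results show that it does not: most of the error there comes from using a t-test on skewed data with unequal groups. The skewness of the analysed change is itself an inference from the volume formula and the admission of large lesions.

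What the reply does not do is give the F-test a benefit. On normal data Welch stays near 5% in every scenario, and at equal sizes it matches the pooled test almost exactly. The objection is to a method that the article states, so it is not a complaint about detail left to an analysis plan.

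**Conclusion.** The point holds as a minor one. The preliminary F-test is a poor selector because it responds strongly to non-normality. The resulting two-stage rule departs from 5% when sizes and variances both differ.

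The departure is about 1.5 points upward (6.5% against 5.0%) or 0.9 points downward (4.1% against 5.0%) under the assumed 50 v 20 split, normal data and 5% levels. It shrinks as the HIFU number approaches 20. It is immaterial at the planned 50 v 50. The SDs, the test levels and the HIFU number at the first comparison are assumptions, not figures from the article.

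**What to change.** In Outcome measures, delete the F-test sentence and state that the between-group comparison of volume reduction uses the Welch (unequal-variance) t-test. This removes one sentence and names one test. At equal sizes it loses essentially nothing, and it makes the choice of test independent of the data. It also makes the HIFU number at the first comparison immaterial to which t-test is used.

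If skewed volume change is a worry, deal with it separately through the scale of the outcome, for example relative change from baseline or the log of the follow-up to baseline volume ratio. A log scale would need a stated rule for lesions that are no longer visible, whose volume would be zero.
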